# Detailed statistical analysis plan for a guided self-determination intervention versus an attention control for outpatients with type 2 diabetes in the randomised OVERCOME trial

**DOI:** 10.1186/s13063-024-08589-6

**Published:** 2024-11-11

**Keywords:** Diabetes, Guided self-determination, Self-determination theory, Autonomy-supportive, Diabetes distress, Depression, HbA1c

## Abstract

**Background:**

Autonomy-supporting interventions may be a prerequisite to achieve better long-term management of type 2 diabetes. Evidence suggests that the guided self-determination (GSD) method might improve haemoglobin A1c and diabetes distress in people with type 1 diabetes. The evidence of an effect of a GSD intervention compared with an attention control group in adults with type 2 diabetes is unknown.

**Methods/design:**

The trial is designed as a pragmatic, investigator-initiated, dual-centre, randomised, parallel-group, assessor-blinded, superiority clinical trial of persons with type 2 diabetes. A nurse will administer GSD intervention versus an attention control. The primary outcome is diabetes distress, and secondary outcomes are quality of life, depressive symptoms, and non-serious adverse events. Exploratory outcomes are haemoglobin A1c, motivation, and serious adverse events. Participants are assessed at baseline, 5-, and 12-month follow-up. Here, we present a detailed, comprehensive plan of all statistical analyses, including methods to handle missing data, and assessments of the underlying statistical assumptions. The statistical analyses will be conducted independently by two statisticians following the present plan.

**Discussion:**

To mitigate the risk of analysis bias and increase the validity of the OVEROME trial, this statistical analysis plan was developed prior to unblinding of the trial results in concordance with the Declaration of Helsinki and the Conference on Harmonization of Good Clinical Practice Guidelines.

**Trial registration:**

ClinicalTrials.gov NCT 04601311. Registered on October 2020.

**Supplementary Information:**

The online version contains supplementary material available at 10.1186/s13063-024-08589-6.

## Background

Type 2 diabetes management aims to prevent and reduce complications of diabetes. Diabetes self-management care depends among other factors on the motivation and autonomy of the person with diabetes. Accordingly, autonomy-supporting interventions might be crucial in achieving engagement and long-term improvement in people with type 2 diabetes through shared decision-making and collaborative goal setting [1]. A method designed to promote autonomy and diabetes self-management skills in people with type 2 diabetes is the empowerment-based method, the GSD method [2–4]. Evidence suggests that the GSD method might improve serum haemoglobin A1c (HbA1c) and reduce diabetes distress in people with type 1 diabetes [5]. However, the effect of GSD on diabetes distress in people with type 2 diabetes is currently unclear and existing evidence is prone to systematic as well as random errors [6, 7].

The OVERCOME trial is a pragmatic, investigator-initiated, dual-centre, randomised, parallel-group, assessor-blinded, superiority clinical trial of persons with type 2 diabetes, designed to assess the benefits and harms of GSD applied in outpatient clinics [6]. It is the recommendation of the Helsinki Declaration [8] and the International Conference on Harmonization of Good Clinical Practice (ICH-GCP) that clinical trials are analysed according to a predefined statistical plan to counteract data-driven analysis results and selective reporting. Here, we describe the detailed statistical analysis plan for the primary, secondary, and exploratory outcomes in the OVERCOME trial [6]. The main publications of the trial results will adhere to this plan.

## Methods

For a detailed description of the trial design and methods, we refer to our trial protocol [6]. The trial population are persons with type 2 diabetes treated at the Department of Endocrinology, the University Hospital of Copenhagen—Rigshospitalet, The Capital Region of Denmark and Steno Diabetes Centre Odense, Odense University Hospital, The Southern Region of Denmark. The participants are eligible for inclusion if they fulfil the inclusion and none of the exclusion criteria below.

Inclusion criteria:Being 18 years of age or older.Having been diagnosed with type 2 diabetes for 3 months or more according to the International Classification System of Diseases (ICD11.2–11.9).Having signed informed consent.

Exclusion criteria:Pregnancy: women who are premenopausal will be asked if they are pregnant or are planning pregnancy prior to inclusion.Prior participation in GSD course(s) for the past 2 years.Lack of signed informed consent.

The trial adheres to our published protocol [6] and the Helsinki Declaration. The trial has been registered at ClinicalTrials.gov (NCT04601311, October 2020) and the Danish Data Protection Agency (P-2020–864, January 2020). The Ethics Committee of the Capital Region of Denmark reviewed the trial protocol but exempted the trial protocol from full review (H-20003638, August 2020). For reporting of this statistical analysis plan, we adhered to the ‘Guidelines for the Content of Statistical Analysis Plans in Clinical Trials’ [9].

### Randomisation and blinding

Participants are randomised centrally at a 1:1 ratio using a web-based system developed and administered by the Copenhagen Trial Unit. The allocation is computer-generated through permuted blocks of varying sizes and concealed from the investigators. Due to the nature of the intervention, the allocation is not blinded to the investigators. The certified GSD nurses enrol the participants and assign the intervention. The randomisation is stratified according to centre and sex.

Participants and treatment providers will not be blinded to the allocated trial intervention due to the difficulties of blinding psychological interventions [10]. The treatment providers will not be involved in the analyses. The outcome assessors, the statisticians at the Copenhagen Trial Unit, and the decision-makers regarding the reporting and conclusions will be blinded to the participants’ allocation.

## Trial interventions

### Experimental intervention

The GSD is a theory-based problem-solving method to overcome barriers related to diabetes management and collaborative care [3]. The method strives to strengthen autonomous motivation, empowerment, and self-determination by focusing on life-illness integration, the relational potential for change, and shared decision-making [4].

The focus areas of the method are embedded in the reflection sheets for the person with type 2 diabetes to work with at home or online. Experienced nurses are certified in the GSD method including advanced communication techniques such as mirroring, active listening, and value-clarifying questions to promote autonomous reflection. Experienced diabetes nurses certified in the GSD method provide two to five sessions every second week after randomisation, as a need-based and thus stepped-care intervention to each participant individually. The sessions are conducted face to face, by video, or over the telephone. The stepped-care intervention is provided as a digital version, an analogue GSD (in paper), or a mixed version as preferred by the participant. The GSD intervention requires participants to complete 13 reflection sheets in a predefined order as preparation for five individual sessions [6]. For further information, we refer to our protocol [6].

### Control intervention

The participants in the control group receive an attention control intervention that include two to five needs-based sessions with a communication-trained medical student or a psychology student, who were all certified counsellors. The needs-defined sessions are scheduled concurrently with the sessions in the experimental group, namely 2 weeks, 4 weeks, and 6 weeks after randomisation. All sessions last up to 1 h. The sessions are conducted face to face, by video, or over the telephone [6].

### Baseline data

Socio-demographic data (age, sex, civil status, educational level [11], employment status, diabetes-related comorbidities, psychiatric comorbidities, medical comorbidities, and diabetes medication) will be presented in a table.

### Outcomes

According to our protocol, outcomes were defined as primary, secondary, or exploratory. This paper describes the detailed analysis plan for all outcomes.

Primary outcome:Diabetes distress assessed by the validated 20-item scale of diabetes-related distress burden, problem areas in diabetes (PAID) [12], at 12 months after randomisation.

Secondary outcomes:Depressive symptoms assessed by the hospital anxiety and depression scale (HADS) [13], at 12 months after randomisation.Quality of life (QOL), assessed as the SF-36 mental component score and physical component score [14, 15] at 12 months after randomisation.Adverse events assessed by the negative effect questionnaire (NEQ)-20 [16, 17]. NEQ-20 is assessed at 12 months after randomisation.

Exploratory outcomes:HbA1c concentration at 12 months after randomisation.Type of motivation regarding diabetes self-care practices assessed by the treatment self-regulation questionnaire (TSRQ), at 12 months after randomisation:◦ Autonomous◦ Controlled (external)◦ Resigned (amotivated)Proportion of participants with at least one serious adverse event in the intervention period, defined according to the International Harmonisation of Good Clinical Practice (ICH-GCP), assessed 12 months after randomisation.

### Sample size calculation

This randomised clinical trial is designed to evaluate superiority when comparing the intervention group and the attention control group. The sample size calculation was based on our primary outcome and an estimated minimal clinical important difference from the mean of six points and standard deviation (SD) of 16 points from our systematic review conducted prior to initiating this OVERCOME trial [7, 18].

With a power of 80% (a beta at 20%) and an alpha at 5%, two-tailed, a sample size of 112 participants is needed in each intervention group corresponding to a total of 224 participants included in the trial.

### Power calculations for the secondary outcomes

For the secondary outcome depressive symptoms, measured by HADS, we chose an estimated minimal important difference of three points and a SD of six points based on the total scale applied in previous trials [19, 20], which correspond to a power of 96.3%.

For the secondary outcome QOL, measured by SF-36, we chose an estimated minimal important difference of six points and SD of 15 points based on previous trials [14, 15], which correspond to a power of 84.9%.

For the secondary outcome adverse events, measured by NEQ-20, we pragmatically chose an estimated minimal important difference of five points and a SD of 13 points [16, 17], which correspond to a power of 82.1%.

### General analysis principles

Statistical analyses will be performed using the latest stable version of R (R Core Team, Vienna, Austria) and/or Stata (StataCorp, LLC, TX, USA) [21]. All valid assessments from every randomised participant will be analysed according to the intention-to-treat principle. Discontinuations and drop-outs and the reasons for these will be reported. Though hypothesis-generating only, we will consider performing a per protocol analysis, if the number of participants who drop-out prematurely exceeds 5% of the total trial population. In the per protocol analysis, which is exploratory, we will include all participants that attended ≥ 2 visits according to our definition of adherence (see section ‘ Handling of missing data’).

### Statistical analysis

#### Continuous outcomes

Continuous data will be presented as means and 95% confidence intervals in figures and tables. The outcomes will be analysed using linear regression analyses adjusted for baseline values of the outcomes: diabetes distress, depressive symptoms, quality of life, HbA1c, motivation (autonomous, controlled, resigned), and the stratification variables (centre and sex).

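### Providers are nested within arm, but no analysis allows for provider clustering; if the provider ICC for PAID is positive, the planned standard error is too small by an unknown amount

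*SAP article*

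**What the plan says.** Randomisation is by individual: "Participants are randomised centrally at a 1:1 ratio" (Randomisation and blinding), stratified by centre and sex. Delivery is also individual, by different people in the two arms. In the GSD arm, "Experienced diabetes nurses certified in the GSD method provide two to five sessions every second week after randomisation" (Experimental intervention). In the control arm, participants receive "two to five needs-based sessions with a communication-trained medical student or a psychology student" (Control intervention).

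For continuous outcomes, "The outcomes will be analysed using linear regression analyses adjusted for baseline values of the outcomes" (Continuous outcomes). The same sentence adds the two stratification variables. The section on assessing the statistical assumptions covers interactions, normality of residuals, homogeneity of variance and overdispersion. It does not mention independence of observations. The sample size rests on "an estimated minimal clinical important difference from the mean of six points and standard deviation (SD) of 16 points" and concludes that "a sample size of 112 participants is needed in each intervention group corresponding to a total of 224 participants included in the trial". The article nowhere mentions a provider effect, cluster-robust errors, an ICC or a design effect.

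**The concern.** In a talking intervention, part of the outcome may depend on who does the talking. Participants of one nurse or student may then have correlated outcomes. Because each provider works in one arm only, provider variation does not cancel in the comparison of arms. It adds to the variance of the treatment difference, and ordinary linear regression does not count it. Adjusting for centre removes only the part that lies between the two sites.

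The article gives some reason to think that delivery varied. Its Limitations section says that therapeutic alliance might influence how well the interventions work and was not measured. Its Discussion reports that several nurses were moved to COVID-19 departments and that a strike might have affected the quality of GSD delivery.

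At stake is the primary comparison, the only one that the plan does not class as hypothesis-generating. If its interval is too narrow, differences between a few providers could be read as an effect of the method.

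**Working it through.** **Inputs from the article (Sample size calculation).** Difference 6 points, SD 16, 112 per arm, and "With a power of 80% (a beta at 20%) and an alpha at 5%, two-tailed".

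**Inputs that must be assumed.** The number of providers per arm, k (4 to 20), and the provider ICC for PAID (0 to 0.05). Caseloads are taken as equal and the ICC as the same in both arms. The full 112 per arm are assumed to be analysed.

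**Step 1: the plan's own figure.** For independent participants, n per arm = 2 × [16 × (1.960 + 0.842) / 6]² = 111.6, so 112. Power at 112 is 80.1%. The stated sample size is reproduced under independence, so it contains no hidden allowance for clustering.

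**Step 2: formulas with clustering.**
- Caseload m = 112 / k
- Design effect DE = 1 + (m − 1) × ICC
- True SE / model SE = √DE
- Actual type I error = 2 × [1 − Φ(1.96 / √DE)]
- SE under independence = 16 × √(2/112) = 2.138
- Power = Φ(6 / (2.138 × √DE) − 1.96)

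**Step 3: results (normal approximation, unadjusted SD 16).**

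| k per arm | m | ICC | DE | SE ratio | Type I error | Power |
|---|---|---|---|---|---|---|
| any | – | 0 | 1.00 | 1.00 | 5.0% | 80.1% |
| 20 | 5.6 | 0.01 | 1.046 | 1.023 | 5.5% | 78.3% |
| 20 | 5.6 | 0.05 | 1.230 | 1.109 | 7.7% | 71.6% |
| 10 | 11.2 | 0.01 | 1.102 | 1.050 | 6.2% | 76.2% |
| 10 | 11.2 | 0.05 | 1.510 | 1.229 | 11.1% | 62.7% |
| 4 | 28 | 0.01 | 1.270 | 1.127 | 8.2% | 70.2% |
| 4 | 28 | 0.05 | 2.350 | 1.533 | 20.1% | 44.9% |

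Worked line for k = 4 and ICC 0.05: DE = 1 + 27 × 0.05 = 2.35 and √2.35 = 1.533. Type I error = 2 × [1 − Φ(1.96 / 1.533)] = 20.1%. Power = Φ(6 / 3.278 − 1.96) = Φ(−0.13) = 44.9%.

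**Step 4: interval width.** Under independence the 95% half-width is 1.96 × 2.138 = 4.2 points. With k = 4 and ICC 0.05 the SE is 2.138 × 1.533 = 3.278. A normal quantile would give a half-width of 6.4 points. However, 4 providers per arm leave about 2 × 4 − 2 = 6 degrees of freedom, so t is about 2.45 and the half-width is about 8.0 points. That is wider than the 6-point target difference. These widths use the unadjusted SD. The planned baseline adjustment would shorten all of them by an amount that the article does not give.

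**The case against.** The strongest reply is that the size is unknown and may be trivial. The article states no provider count, caseload or ICC. With 20 providers per arm and ICC 0.01 the test is nearly nominal, and the worst figures need both the fewest providers and the highest ICC. This stands, and it rules out a stronger reading. A reader might infer that each provider treated a large number of participants, so that standard errors are likely too small for every continuous outcome. The article does not support that. Caseloads are not given, the ICC may differ by outcome and could be near zero for HbA1c, for example, and all outcomes other than the primary are declared hypothesis-generating.

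A second reply is that this is an individually randomised trial with individual sessions, and that the ordinary standard error is defensible if inference is meant only for the nurses and students who took part. That is a fair position and a reason to leave the primary model alone. But the article states no such restriction, and it presents its plan as comprehensive and as covering the underlying assumptions.

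A third reply is that provider numbers and allocation belong in the protocol, which is not shown. That is so, and their absence is not criticised here. The point concerns the model, which the article does specify.

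Finally, an analysis with few providers is imprecise. That also stands, so it should inform the reading of the primary result and not override it.

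**Conclusion.** The point holds as an unaddressed risk to the primary analysis, of unknown size. Provider is nested within arm, the PAID model treats participants as independent, and no other analysis checks the consequence. Any positive provider ICC for PAID that remains after adjustment for baseline, centre and sex makes the planned standard error too small when inference is meant to extend beyond the providers used. Over the assumed range of 4 to 20 equally loaded providers per arm and ICC 0 to 0.05, the effect runs from none to a type I error of about 20% and power of about 45%. The article does not show where in that range the trial lies. It therefore does not establish that the primary result will be wrong, only that the plan offers no means of telling whether that result withstands provider clustering.

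**What to change.** Keep the primary model. Under Continuous outcomes, add one prespecified sensitivity analysis of PAID at 12 months:

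- Use the same linear model with a random intercept for provider nested in arm, fitted by restricted maximum likelihood with small-sample degrees of freedom (Kenward–Roger or Satterthwaite). Provider fixed effects would not work, because they cannot be separated from arm.
- Assign each participant to the provider of the first attended session. This settles the case of participants who changed nurse. Treat each participant with no session as a single-person cluster, so that non-attenders are not given a shared effect.
- Report the number of providers per arm, their caseloads and the estimated ICC.
- Show the resulting interval beside the primary one, and say in the discussion of the primary result whether the conclusion is robust to provider clustering.

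The cost is one extra model and no new participants. It requires that the treating provider was recorded, which the article does not confirm. With few providers the ICC will be imprecise and the interval may be clearly wider, as Step 4 shows. The addition should be made before unblinding; after that it should be labelled post hoc.

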#### Dichotomous outcomes

Dichotomous outcomes will be presented as proportions for each group and will be analysed assuming a binomial distribution using the generalised linear model with a log link adjusted for centre and sex. If the analysis does not converge, binary data will be analysed using logistic regression, and the NLCOM command [21] will be used to obtain relative risks (RRs) and 95% confidence intervals of the RRs. Similar methods will be used for analysis in R; however, 95% confidence intervals will be bootstrapped.

#### Handling of missing data

Missing data will be handled according to the recommendations of Jakobsen et al. [22]. In short, all randomised participants (the intention-to-treat population) will be included in the primary analysis of all outcomes. If the missing data exceeds 5%, we will consider using multiple imputations and perform the best–worst/worst-best case scenarios to assess the potential range of impact of the missing data. As this is a stepped care intervention, adherence to the interventions is defined as having attended two–five sessions. Any deviations from protocol will be summarised in the section ‘deviations between the protocol and the trial’.

#### Early stopping

If we are not able to recruit and randomise the full sample size of 224 participants, the statistical significance level will be adjusted according to the Lan-DeMets sequential monitoring boundaries based on O’Brien-Fleming alpha-spending function [23–26]. The Lan-DeMets-O’Brian-Fleming method for sequential monitoring is able to take the accrued sample size distance to the planned sample size into consideration to reduce the risks of false positive findings if we are not able to achieve the planned sample size [26, 27]. We will only use this analysis once if we do not reach our sample size.

This will be applied for the primary and secondary outcomes: diabetes distress, depressive symptoms, and quality of life. Similarly, the primary confidence intervals presented will be the adjusted confidence interval. Furthermore, we will use the minimal important differences defined above. Finally, outcomes where adjusted confidence intervals are presented will also have 95% confidence intervals presented in the supplemental material.

#### Correction for multiplicity

We assess only one primary outcome and consider all other outcome results as hypothesis-generating only. Therefore, we have used a two-sided alpha of 5% as the acceptable risk of type I error in the sample size and power estimations.

#### Assessment of underlying statistical assumptions

We will assess the statistical assumptions underlying each statistical method following the commendations of Nørskov et al. [28]. In short, for all regression analyses, we will test for major interactions between each covariate and the intervention variable. When assessing for major interactions, we will, in turn, include each possible first-order interaction between included covariates and the intervention variable. For each combination, a significant interaction is only evident if the interaction is statistically significant after Bonferroni adjusted thresholds (0.05 divided by the number of possible interactions, if any interaction exits).

For the assessment of the underlying statistical assumptions for the linear regression, we will inspect quantile–quantile plots of the residuals for normal distribution and assess for homogeneity of variances by using residuals plotted against covariates and fitted values. If deviations from model assumptions are present, we will consider log or square root transformation.

To consider a potential overdispersion, we will assess if the deviance divided by the degrees of freedom is significantly > 1.0. In this case, we will consider using a maximum likelihood estimate of the diversion parameter.

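### The plan leaves the scale of the primary PAID analysis open to a log or square-root change after residual plots are seen, without keeping the mean difference in points as the primary result

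*SAP article*

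**What the plan says.** - **Outcome.** The primary outcome is "Diabetes distress assessed by the validated 20-item scale of diabetes-related distress burden, problem areas in diabetes (PAID"), measured at 12 months (Outcomes). The scale's range is not stated.
- **Design target.** The trial is sized on "an estimated minimal clinical important difference from the mean of six points and standard deviation (SD) of 16 points" (Sample size calculation), in raw PAID points.
- **Model.** Continuous outcomes go into a linear regression adjusted for the baseline value, centre and sex, and are reported as means with 95% confidence intervals (Continuous outcomes).
- **Remedy.** After inspection of quantile–quantile and residual plots: "If deviations from model assumptions are present, we will consider log or square root transformation" (Assessment of underlying statistical assumptions). The section does not say what counts as a deviation, which transformation comes first, how a result would be returned to points, or whether the untransformed result stays primary.
- **Reuse of the target.** If recruitment falls short of 224: "Furthermore, we will use the minimal important differences defined above" (Early stopping). That section covers diabetes distress, depressive symptoms and quality of life.
- **Safeguards.** Two statisticians analyse data with arms labelled A and B. The steering committee decides between them if they differ, and the reasons and reports are published (Statistical reports).

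**The concern.** The sample size, the presentation of results and the shortfall rule all use the mean difference in points. The remedy for poor residuals can move the primary analysis to a scale on which that quantity is not estimated, and the decision is taken after the trial data have been seen.

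Two things are at stake. First, the coefficient from a transformed model cannot be read directly against six points. Second, the hypothesis changes: equal arithmetic means do not imply equal geometric means or equal mean roots when the spread differs between arms. Unequal variance is one of the deviations for which the plan offers a transformation, so the remedy may be applied in the very setting where it can mislead about mean distress.

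**Working it through.** **1. The plan's own figure.** Inputs from Sample size calculation: difference 6, SD 16, two-sided alpha 5%, power 80%. Allocation is 1:1 (Randomisation and blinding).

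n per arm = 2 × SD² × (z₀.₉₇₅ + z₀.₈₀)² / difference² = 2 × 256 × (1.960 + 0.842)² / 36 = 111.6, so 112. Power at 112 per arm is 80.1%. The stated figure reproduces (a t-based calculation gives 112.6), and it is tied to raw points.

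**2. Six points on the other scales.** The plan gives no expected PAID mean, so control means m of 20 to 50 are assumed. Ratio = (m − 6)/m; log difference = ln of that ratio; root difference = √(m − 6) − √m.

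| Assumed control mean | Ratio | Log difference | Root difference |
|---|---|---|---|
| 20 | 0.70 | −0.36 | −0.73 |
| 30 | 0.80 | −0.22 | −0.58 |
| 40 | 0.85 | −0.16 | −0.49 |
| 50 | 0.88 | −0.13 | −0.44 |

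Conversely, a ratio of 0.80 means 4, 6, 8 or 10 points at these four means. No single transformed effect stands for six points.

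**3. Equal means, unequal spread.** Assume gamma-shaped scores with mean 25 in both arms, SD 16 in one and 20 in the other. Shape k = (mean/SD)²: (25/16)² = 2.44 and (25/20)² = 1.56. Scale θ = 25/k: 10.24 and 16.

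- Geometric mean = θ·exp(ψ(k)), ψ being the digamma function: 20.1 and 17.6, a ratio of 0.87.
- Mean root = √θ·Γ(k + ½)/Γ(k): 4.75 and 4.62.
- Arithmetic means: 25 and 25, a difference of zero.

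So the transformed models have a real difference to find where mean distress does not differ. Simulated rejection rates at the 5% level (112 per arm, scores rounded to steps of 1.25 and limited to 0–100, 20,000 trials, two-group t-test) were:

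| Analysis | Rejected |
|---|---|
| Raw points | 5.0% |
| Square root | 9.1% |
| Log(x + 1) | 18.8% |

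A repeat with unequal-variance t-tests (10,000 trials) gave 5.1%, 9.0% and 18.9%. A baseline-adjusted version, closer to the planned model, gave about 5% for raw-scale least squares and for HC3, against 12% (square root) and 27% (log(x + 1)). Those last two figures depend on the assumed correlation between baseline and follow-up.

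**4. Is a transformation needed for skewness alone?** With identical gamma distributions in both arms (SD 16, assumed means 20, 25 and 30), raw-scale type I error was 4.9%, 5.0% and 4.9%. In these settings it was not needed to protect the test.

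**5. How often the scale would decide the result.** In the same null simulations, raw and log(x + 1) disagreed on significance in 3.9%, 3.8% and 3.1% of trials. Taking the most favourable of raw, square root and log(x + 1) gave type I error of 6.4% to 7.0%. That is a worst case and is not what the plan says will be done.

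**6. Zero scores.** If PAID can score zero (an assumption), log is undefined there and needs an offset, which the plan does not give. The expected number of zeros among 224 depends heavily on the assumed mean and shape: over means of 15 to 35, about 0 to 13 for a gamma shape and 4 to 41 for a normal shape cut at zero. Square root is defined at zero.

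**The case against.** The strongest reply is that the plan commits only to considering a transformation, and only if deviations appear. The named method is linear regression reported as means, and transforming after residual checks is conventional. The section is also a short summary of a cited methods paper that may hold more detail. All of this is fair. It makes the change possible rather than certain, but nothing in the article keeps the point-scale result primary if the option is used.

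The safeguards are real. Masked arms limit a choice that favours one treatment, and published reports with reasons would expose a difference between the analysts. They do not fix the scale in advance, and the article's Limitations section concedes that the masking is incomplete.

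Four stronger readings are tempting and not supported:

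- **That a transformed result could never be compared with six points.** A prespecified back-transformation or standardisation to points could restore the comparison. The plan simply has none.
- **That log is known to fail on these scores.** The article gives no range for PAID or NEQ-20, so zeros are an assumption.
- **That the trial was sized on NEQ-20 as well.** It was sized on PAID alone. NEQ-20 has only a secondary power calculation, and Early stopping does not list it.
- **That raw-scale analysis has been shown safe in all cases.** The simulations use assumed gamma scores, and most are unadjusted. They support the raw scale in those settings only.

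**Conclusion.** The point stands as a gap in what the plan fixes: the effect scale of the primary outcome stays open until residual plots of trial data have been seen, while the design target and the shortfall rule are in points. The possible consequence is material. In the example with equal means and SDs of 16 and 20, the transformed analyses rejected in 9% to 19% of trials unadjusted and 12% to 27% baseline-adjusted, against about 5% on the raw scale. These sizes rest on an assumed mean of 25, gamma-shaped scores and a 0–100 range. The change of target itself rests on none of them, since a ratio of geometric means and a difference in mean roots are not a difference in means. The sample size of 112 per group is not in error. This should be corrected before unblinding, and it takes little work.

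**What to change.** Add to Assessment of underlying statistical assumptions: the baseline-adjusted mean difference on the original scale remains the primary result whatever the residual plots show, with heteroscedasticity-consistent (HC3) or bootstrap confidence intervals; any log, square-root or rank-based analysis is a labelled sensitivity analysis. The choice between HC3 and bootstrap should be made now, so that both statisticians use the same one. If a log sensitivity analysis is kept, state the offset to be used should zeros occur.

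Cost: a sentence or two in the plan. Intervals may be marginally wider if variances are in fact equal. The sample size stays at 112 per group.
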